### Allocation of participants to trial groups

Potential confounding variables will be controlled by randomization. The unit of randomization will be the CPHSS with stratification by urban or rural setting [27]. For CPHSS enrollment, 2 random lists will be prepared to establish the order in which CPHSSs will be contacted. We will follow this order systematically until the enrollment of 4 urban and 12 rural CPHSSs is complete.

A second randomization will occur after participants have completed their baseline measures. This randomization will be stratified to minimize the differences within groups due to geographic location. Thus, 2 urban and 6 rural CPHSSs will be allocated to each group. Randomization and allocation will be done using computer software, and data will be entered by an experienced, independent biostatistician.

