### Outcome measures

The primary outcome of interest is the assumed role in the decision making. We will use the modified version of the Control Preferences Scale [28] designed to assess the assumed role in the decision-making process reported by the client or the caregiver [29]. The scale consists of a single question to assess the client’s perception of locus of control over the decision-making process. This is the scale used most in studies assessing the implementation of SDM in clinical practices [18,30]. It is responsive to change and correlates with patients’ as well as with clinicians’ reported levels of patient involvement [31]. Response options (n = 5) are as follows: A) I made the decision; B) I made the decision after seriously considering my providers’ opinions; C) My providers and I shared the responsibility for the decision making; D) My providers made the decision after seriously considering my opinion; E) My providers made the decision. A and B represent a client-controlled decision-making process, C represents a shared decision-making process, and D and E represent a practitioner-controlled decision-making process [29]. We will combine A, B and C to identify the proportion of clients reporting an active role in the decision-making process, and we will combine D and E to identify a passive role. We will perform our analysis by assessing the increase in the percentage of clients reporting an active role.

Measures of secondary outcomes will be collected. More specifically, in clients and caregivers, we will assess their preferred and chosen option (remain at home or move to care facility); decisional conflict using the Decisional Conflict Scale [32,33]; decisional regret using the Decisional Regret Scale [34]; HR-QoL (only in client) using 2 subscales from the Nottingham Health Profile: Social Isolation and Emotional Reactions [35-38]; and burden of care (only in caregivers) using a validated scale [39-42].

In providers, at study entry and exit, we will assess their intention to engage in SDM behaviors in the context of an IP home-care team sharing the decision with elderly people about whether to stay at home or move to another location.

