### Statistical consideration

#### Sample size

The primary outcome of interest is the proportion of elderly people who report an active role in the decision-making process regarding whether to stay at home or move to a care facility. Our estimate of the sample size is based on our updated reviews of interventions to improve the uptake of SDM [43] and earlier studies in primary care, in which we observed a 20% absolute difference between groups with an expected baseline value of 50% for the active role [44]. Our biostatisticians provided a number of scenarios with ICCs ranging from 0.02 to 0.05 and the number of clusters ranging from 12 to 16. We used a conservative value of ICC of 0.05 as the upper limit. In order to detect a difference of 20% (50% to 70%) between the intervention group and the control group after the intervention with 80% power, and a 5% significance level, we would require a total of 186 clients for an individually randomized trial. In considering an ICC of 0.05 and 16 clusters (CPHSSs), we would need a sample size of 456 clients in total. Allowing for a 10% loss to follow-up, 501 clients will be recruited (32/CPHSS). We will also recruit 5 clients/CPHSS before the intervention. This is deemed a sufficient number to be able to compare CPHSSs (experimental versus control) at trial entry on the basis of their clientele profiles [45].

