#### Analysis plan

We will perform a descriptive statistical analysis of organizational (CPHSS/health professionals) and socio-demographic (clients/health professionals) characteristics in order to assure the comparability of the intervention and control groups. Potentially confounding variables, if any, will be introduced as covariates in mathematical modeling analysis. Multilevel modeling will be used to take the hierarchical structure of the data into account by specifying random effects at each of the 2 levels: 1) CPHSS and 2) client. For each outcome analyzed, according to the type of variable (continuous or categorical), the goodness of fit and the assumptions of each model will be assessed. Statistical analysis will be performed using the SAS statistical package [46]. The primary outcome, i.e. the proportion of clients reporting an active role in the decision-making process, will be analyzed through multilevel logistic regression using the GLIMMIX procedure of the SAS program. The least squared mean proportions will be estimated and compared to assess the effect of the intervention on the primary outcome. Secondary outcomes will be comparisons between the 2 groups (intervention, control) using multilevel modeling. The *P* value will be adjusted for any multiple comparison tests. Adjustment for multiple comparisons will only be made for secondary outcomes, using the Bonferroni method. This will avoid significant results being due to chance alone. Analysis will be performed after the pre-intervention data collection (for providing performance feedback during the workshop) and at the end of the trial. We will explore the impact of differences between male and female clients on the primary outcome.

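### Secondary outcomes are adjusted by single-step Bonferroni, which is valid but never more powerful than Holm's step-down procedure at the same familywise error

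*Protocol article*

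**What the plan says.** The Analysis plan section names the method outright: "Adjustment for multiple comparisons will only be made for secondary outcomes, using the Bonferroni method". The next sentence gives the only stated reason: "This will avoid significant results being due to chance alone". No step-down or other refinement is mentioned. The number of tests in the family and the familywise level are not given.

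Under Outcome measures, the paragraph that opens with "Measures of secondary outcomes will be collected" lists preferred option, chosen option, decisional conflict, decisional regret, two Nottingham Health Profile subscales (clients only) and burden of care (caregivers only). The paragraph after it adds providers' intention to engage in shared decision making. Counted once each, that is eight comparisons. The count is ours, not the article's.

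The Sample size section powers the primary outcome only, for an active role in 50% of controls against 70% under the intervention: "with 80% power, and a 5% significance level, we would require a total of 186 clients for an individually randomized trial". The adjustment does not apply to the primary outcome.

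**The concern.** This is a method that the article names, so the point is not about a detail left to an unseen analysis plan. For hypothesis testing, the named method is dominated by another that is equally simple. Both need only the p-values and make no assumption about how the outcomes are correlated. Both hold the familywise error at the chosen level. Holm can only add rejections.

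What is at stake is power for the secondary outcomes, and nothing more. Decisional conflict, regret and the option outcomes all concern the same decision, so more than one of them could respond if the intervention works. That is the situation in which Holm gains most. The sample size makes no allowance for an adjustment of the secondary outcomes, so power given up there is not made good elsewhere.

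**Working it through.** **The plan's own figures.** The article states no figure for the secondary adjustment. The primary sample size can be reproduced, which confirms the error rates used below. For 50% against 70%, two-sided 5% and 80% power, with mean proportion 0.60:

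n per arm = [1.960 × √(2 × 0.60 × 0.40) + 0.842 × √(0.50 × 0.50 + 0.70 × 0.30)]² / 0.20² ≈ 93

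That gives 186 in total, as stated. A design effect of 1 + (30 − 1) × 0.05 = 2.45 gives 186 × 2.45 = 455.7, or 456, as stated. The cluster size of 30 is inferred. None of this depends on the secondary adjustment.

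**Inputs.** From the article: the Bonferroni method, the list of secondary outcomes and the trial's 5% significance level. Assumed, because the article does not give them:
- 8 tests in the family (range 6 to 12)
- familywise level 5%
- correlation 0.3 between test statistics
- 80% or 50% unadjusted power for each true effect

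**Thresholds.** For m tests with ordered p-values, Bonferroni compares every p-value with 0.05/m. Holm compares the i-th smallest with 0.05/(m − i + 1) and stops at the first failure. For m = 8:
- Bonferroni: 0.05/8 = 0.00625 for every test.
- Holm: 0.0063, 0.0071, 0.0083, 0.0100, 0.0125, 0.0167, 0.025, 0.05, from the smallest p-value upward.

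Holm's first threshold is Bonferroni's threshold and the later ones are larger. Two things follow. Every Bonferroni rejection is also a Holm rejection. The probability of at least one rejection is the same under both.

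**Power of one test under Bonferroni.** The two-sided critical value at 0.00625 is 2.734.
- 80% unadjusted power means a non-centrality of 1.960 + 0.842 = 2.802, so power is Φ(2.802 − 2.734) ≈ 52.7%.
- 50% unadjusted power means a non-centrality of 1.960, so power is Φ(1.960 − 2.734) ≈ 22%.

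**Simulated average power per true effect** (8 tests, correlation 0.3, 80% unadjusted power):

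| Outcomes truly affected | Bonferroni | Holm | Gain (points) |
|---|---|---|---|
| 1 of 8 | 52.7% | 52.8% | about 0 |
| 2 of 8 | 52.8% | 53.8% | about 1 |
| 4 of 8 | 52.8% | 56.0% | about 3 |
| 8 of 8 | 52.6% | 63.8% | about 11 |

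In the last row this means 8 × 0.526 = 4.2 true effects found on average, against 8 × 0.638 = 5.1. At 50% unadjusted power the gains are 0.4 points (two real), 1.3 (four real) and 4.3 (eight real). Familywise error was at most 4.6% for both methods. In no replicate did Bonferroni reject something that Holm did not.

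**Cross-check on a different basis.** Start from the planned sample instead of a fixed power. The average cluster size is 456/16 = 28.5, the design effect is 1 + 27.5 × 0.05 = 2.375, and the effective sample is 456/2.375 = 192. A standardized effect of 0.4 (assumed) has non-centrality 0.4 × √192 / 2 = 2.77. With 8 tests and correlation 0.3, Bonferroni against Holm is 51.4% against 51.5% (one real), 51.4% against 54.5% (four real) and 51.4% against 62.4% (eight real).

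Over 6 to 12 tests, effects of 0.3 to 0.5 and correlations of 0 to 0.3, the gain is about 0 to 0.1 points with one real effect, 1 to 4 with half real and 3 to 15 with all real. A single effective sample of 192 is a simplification, because caregiver-only and provider outcomes rest on other samples.

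**The case against.** The strongest reply is that nothing here is wrong. Bonferroni holds the familywise error under any dependence, is prespecified, and does what the article wants it to do. That stands: this is an avoidable inefficiency and not an error.

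The larger gain also needs favourable conditions, and three objections to it stand.
- The 11-point figure requires all eight outcomes to be truly affected, each with 80% unadjusted power. The Background calls the decision strongly dependent on preferences, and the article predicts no shift toward home or facility. Preferred and chosen option, two of the eight, are therefore weak candidates for true effects.
- Equal power across outcomes has no basis in the article. Burden is measured in caregivers only, quality of life in clients only, and intention in providers.
- The family is inferred. A reader might conclude that each secondary outcome must reach p < 0.006, but the article fixes neither the number of tests nor the familywise level, so that threshold is an illustration.

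Bonferroni also leads directly to simultaneous confidence intervals, which is a real practical reason to choose it. The article mentions no such intervals. A reader might infer that none are planned, but a condensed article with no analysis plan at hand does not establish that.

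What the reply does not answer is the comparison itself: for testing at the same familywise error, Holm never does worse.

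**Conclusion.** The point holds as an optional improvement of low severity. On the assumptions of 8 tests, familywise 5% and correlation 0.3, the gain in average power runs from about 0 points (one real effect) to about 11 (all eight) at 80% unadjusted power, and from about 0.4 to 4 points for two to eight real effects at 50%. The article does not allow a narrower figure.

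A reader might infer that Bonferroni will cause real secondary effects to be missed. The article does not support that as a flat statement. The two methods can differ only after a first rejection, and if one outcome responds they are practically the same. The primary outcome, its significance level and the sample size are untouched.

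**What to change.** In the Analysis plan, name the Holm step-down method at familywise 5% in place of Bonferroni for the secondary outcomes, and report Holm-adjusted p-values. For the i-th smallest of m p-values, the adjusted value is the largest of (m − j + 1) × p(j) over j = 1 to i, capped at 1. Make the change before any outcome data are seen by group, so that results cannot drive the choice.

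The cost is one phrase. No extra clients, data or models are needed, and no rejection that Bonferroni would make is lost. The p-values from the separate secondary models must be brought together for the adjustment. The one drawback is that simultaneous confidence intervals matching Holm are less direct than Bonferroni intervals, which matters only if such intervals are wanted.

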### Compliance

We will reinforce compliance with the intervention by i) sending reminders before the training in SDM; ii) providing interactive workshops in each of the participating IP home-care clinical sites at a time convenient for providers; iii) offering continuing professional development credits; and iv) monitoring the number of participants accessing and completing knowledge scores in the online tutorial. Compliance with correct completion of questionnaires will be reinforced by detailed instructions provided by the research assistant beforehand and verification of the completed questionnaires by the research assistant afterwards. We will gather detailed information on the flow of participants throughout the trial.

### Losses to follow-up

We expect few losses to follow-up in this trial due to the stability of the population studied, only one data collection point for clients and caregivers, and additional measures to minimize loss. All study participants will be included in the analysis as part of the group to which they were randomized, regardless of whether they completed the study or not (‘Intention-to-treat’ analysis). ‘Worst-case scenario’ sensitivity analysis will be performed for missing data on clients.

### Trial steering committee

The trial steering committee will include all co-principal investigators (FL, DS and NB), the project coordinator (AF), a biostatistician and one caregiver representative. Given the integrated knowledge approach underlying this trial and the nature of the trial, we do not plan to have a data monitoring committee. Research assistants will be instructed to report any adverse events or unintended effects of the trial interventions or trial conduct.

### Dissemination policy

All stakeholders have been directly involved in designing our IP-SDM model and intervention and providing feedback to make them more relevant to the home-care setting. All team members will contribute to the dissemination of study results. We will tailor effective knowledge translation strategies for each targeted users’ group (for example, policy makers, clinicians, healthcare organization managers, seniors’ associations). We will disseminate study results a) at conferences (scientific and professional) whose themes relate to SDM, IP and health policy; b) on the websites of team members; and c) as articles in peer-reviewed journals and professional journals.

## Discussion

We have described the methods that we will use to evaluate the impact of training interprofessional home-care teams in shared decision making combined with a decision aid on the proportion of elderly people who report being active in the decision-making process regarding whether to stay at home or move to a care facility. Results from this trial will lay the groundwork for a national strategy regarding the improvement of the decision-making process for the significant numbers of aging Canadians who are facing a potential transition to care facilities and for their caregivers. Furthermore, skills gained by participants in the intervention arm of this study are likely to be transferable to supporting clients who are making other decisions, such as those relating to mental health. Thus, the results of the proposed trial will concretely address identified challenges and knowledge gaps: 1) the growing number of aging Canadians facing the decision regarding the location of care who need client-centered decision support; 2) the need for improvement of the decision-making process regarding the location of care; 3) the need for a framework to guide IP home-care teams in this process; and 4) the need for training in this process [47]. This project will help IP home-care teams in providing the highest quality of care for seriously ill elderly people and in providing support for their families.

## Trial status

Client recruitment started on 14 October 2014, and we anticipate recruitment will be completed in March 2016.

## Abbreviations

CPHSS: center for primary healthcare and social services
CSSS: Centre de santé et de services sociaux
IP: interprofessional
IP-SDM approach: interprofessional (IP) approach to SDM
SDM: shared decision making
